### Study procedures

Data collection will take place from February 2011 till August 2011. During this period, patients presenting following an acute traumatic injury of the wrist will receive care as usual. The difference is that, upon presentation with wrist pain following trauma, an additional Case Report Form (CRF) containing multiple clinical parameters will be completed by the treating physician. These clinical parameters are defined by trauma-mechanism, physical examination and functional testing and include; mechanism of trauma; swelling of the distal radius, swelling of the Anatomical Snuffbox; visible deformity of the wrist; palpability of radial artery pulsations; pain on palpation of the distal radius, distal ulna, Anatomical Snuffbox, radial styloid, ulnar syloid and Lister's tubercle; pain on dorsal flexion, palmar flexion, supination, pronation ulnar deviation, radial deviation; difference in prehensile strength test between affected and unaffected side; outcome distal radial drawer test and pain on axial compression (see appendix). Radiographs of the distal radius will be performed according to Dutch guidelines; at least one posterior anterior (PA) and one lateral view with the elbow in 24 degrees of flexion. Additional imaging for injuries associated with wrist trauma, e.g. suspected fracture of the scaphoid, can be performed selectively and will be on account of the treating physician. The independent radiologist assessing the outcome using the reference standard (X-rays) will be blinded from the results of the CRF to prevent incorporation bias. The dichotomous nature (yes/no) of the CRF and the fact that it is a standardized way of history taking and examination, will decrease interobserver variability and thus minimize underestimation of the potential diagnostic value of the parameters.

Upon completion of the data collection in all three participating medical centers, a prediction rule will be developed based on data from two of the participating hospitals; the academic hospital and the non-academic teaching hospital. Since prediction rules always perform perfectly in the patient population they were generated from, a validation study in a new study population is required to assess its predictive quality. To ensure the most stringent form of validation, the rule will be validated in data from the third hospital, the non-teaching hospital. This method is also known as domain validation. The method of data collection in the third hospital will be similar and done simultaneously. This dataset will be comparable to the first regarding size and informative parameters and the model will be tested to verify its predictive value of the primary outcome: distal radius fracture. If necessary, the model will be updated and finally it will be presented as a simplified risk score.

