In 2003, Cevik et al. evaluated the value of physical findings to predict fractures in patients with acute wrist trauma [8]. They included fifty-five patients in their study and concluded that edema, pain on grip and supination, pain on active and passive motion and localized tenderness can be valuable to predict a fracture.

Recently, Calco-Lorenzo et al. analyzed the possibility of creating a clinical decision rule for the assessment of conventional X-rays in acute wrist trauma [9]. They employed 46 different anamnestic and examination variables and included 179 patients in their study. They concluded that an age equal or higher than thirty-five, edema in the dorsum of the wrist, limited supination or radial deviation as compared to the contralateral wrist and pain on performing the distal radioulnar drawer test, was predictive of the presence of a distal radius fracture. However, they advised "a broader study should be undertaken to assess the feasibility of introducing a clinical decision rule".

Therefore, the primary aim of this study is to formulate a clinical decision rule to determine when an X-ray of the distal radius is necessary in patients presenting to the Emergency Department following wrist trauma.

The second aim of this study is to validate this decision rule in a new patient population and to present it as simplified risk score.

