#### Inclusion criteria

• Patient aged 18 years and older

• An acute trauma of the wrist (< 72 hrs following trauma)

• Pain on pressure in wrist area

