#### Sample size

Due to the multivariable character of this study, a sample size calculation is not applicable, and we will therefore use a convenience sample. A common guideline is that the number of potential determinants should not exceed 10% of the number of events, in this case distal radius fractures. The Case Report Form (CRF, additional file 1) lists 20 parameters, therefore requiring a minimum of 200 patients with a distal radius fracture (see appendix). In preparation of this study, we recently conducted a retrospective study in the participating hospitals to determine the number of X-rays performed for wrist trauma. In the academic hospital, it was found that 550 radiographs in patients with acute wrist trauma were performed during a one year period. In the non-academic teaching hospital, this figure was even higher: 2300 in one year. The percentage of radiographs which reveal a distal radius fracture is currently being determined in a separate study performed at these hospitals and is estimated to be about 50%. We expect that a period of six months will suffice to include enough patients (500) to formulate the decision rule. No strict guidelines for the required sample size of external validation studies exist. However, we aim to perform this analysis in a dataset which is of equal size as the development data set. Therefore, to validate the decision rule in a new population, this data will be collected simultaneously in the third hospital, the non-teaching hospital, using the same approach as in the other two hospitals.

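### Age is not among the 20 candidate predictors, although the protocol cites it as predictive and eligibility requires it to be known

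*Protocol article*

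**What the plan says.** The Abstract and the Study procedures section draw the predictors from three domains: how the injury happened, physical examination, and functional testing. The full sentence in Study procedures begins "These clinical parameters are defined by trauma-mechanism, physical examination and functional testing and include; mechanism of trauma" and ends "outcome distal radial drawer test and pain on axial compression (see appendix". There is no demographic domain.

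The Sample size section says that the case report form (CRF) "lists 20 parameters, therefore requiring a minimum of 200 patients with a distal radius fracture". It rests this on the guideline that "the number of potential determinants should not exceed 10% of the number of events". On recruitment it states: "We expect that a period of six months will suffice to include enough patients (500) to formulate the decision rule". The share of radiographs showing a distal radius fracture "is estimated to be about 50" per cent.

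The Background summarises a 179-patient study that screened 46 variables for a wrist X-ray rule: "They concluded that an age equal or higher than thirty-five, edema in the dorsum of the wrist", followed by two further kinds of examination finding. Elsewhere age appears only as an eligibility limit: "Patient aged 18 years and older".

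The Statistical analysis section describes logistic regression, reduction by likelihood ratio test and, if needed, updating of the intercept in the third hospital. It names no additional candidate variables.

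**The concern.** The protocol offers the earlier study as part of its rationale and carries most of its findings forward. Dorsal swelling, supination, radial deviation and the drawer test each have a counterpart on the new list. Age, which comes first in that study's findings, has none, and no reason is given.

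This is more than a missing detail, because the candidate set limits everything that follows. Reduction by likelihood ratio test can only remove variables. Updating the intercept can correct the average risk in a new hospital, but it cannot restore discrimination or correct predictions that are too high in one age group and too low in another. If age does carry information beyond the examination, the rule loses a predictor that needs no examination and is not subject to the interobserver variability that Study procedures itself raises for the form.

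**Working it through.** **Step 1. Is the list closed?** Items named in Study procedures:

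| Group | Items |
|---|---|
| Mechanism of trauma | 1 |
| Swelling (distal radius, snuffbox) | 2 |
| Visible deformity | 1 |
| Radial artery pulsation | 1 |
| Pain on palpation, six sites | 6 |
| Pain on motion, six directions | 6 |
| Grip strength difference | 1 |
| Drawer test | 1 |
| Axial compression | 1 |
| **Total** | **20** |

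The protocol's own figure is reproduced: 20 parameters x 10 events = 200 fractures. Because the count matches exactly, none of the 20 counted places is left for age.

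**Step 2. Is there room for age?** Inputs from the Sample size section: 500 patients, about 50% with a fracture, 10 events per parameter. Expected fractures = 500 x 0.50 = 250, so the guideline allows 250 / 10 = 25 parameters.

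| Candidates | Fractures needed (10 x k) | Events per parameter (250 / k) | Lowest fracture share in 500 that meets the guideline |
|---|---|---|---|
| 20 (as written) | 200 | 12.5 | 40% |
| 21 (plus age) | 210 | 11.9 | 42% |
| 22 (plus age and sex) | 220 | 11.4 | 44% |

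**Step 3. How much could be lost?** The documents give no effect size, so this step rests on assumptions. Half of the simulated patients have a fracture. The other predictors are summarised as a normal score x with a set AUC, so the separation is d = √2 x Φ⁻¹(AUC). Age 35 or over is present in q0 = 50% of patients without a fracture and in q1 = OR / (1 + OR) of those with one, and is independent of x given fracture status. The combined score adds ln(q1/q0) to d·x when age is 35 or over, and ln((1 − q1)/(1 − q0)) otherwise. With one million simulated patients per scenario:

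| AUC without age | OR 1.5 | OR 2 | OR 3 |
|---|---|---|---|
| 0.75 | 0.754 | 0.763 | 0.780 |
| 0.80 | 0.803 | 0.809 | 0.822 |
| 0.85 | 0.853 | 0.856 | 0.864 |

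The gain runs from about 0.00 (OR 1.5) to 0.03 (OR 3 with a base AUC of 0.75).

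**The case against.** **The CRF is not shown.** The article introduces its items with the word include and refers to an appendix. Age could be recorded administratively, outside the physician's form, and the full protocol might list it. This limits certainty. However, the article sizes the study on exactly the 20 items it names and twice confines the predictors to domains that do not cover age. Recording age would not make it a candidate.

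**The evidence for age is thin.** It is one study of 179 patients with 46 variables screened, a cut at 35 and no effect size quoted. The 55-patient study in the same section does not list age among its predictors. This stands against calling age a strong predictor, but not against testing it.

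**Stronger readings.** A reader might infer four further things that the documents do not support:

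- *That sex is equally a known omission.* No section reports sex as predictive.
- *That the rule will certainly spare fewer X-rays.* The lower end of the simulated range is close to no effect, and overlap between age and the examination findings could shrink the gain further.
- *That omitting age will show up as miscalibration in the third hospital.* Nothing says that the age mix differs there, and the intercept update would absorb an average shift.
- *That the addition is free.* It costs no new examination, but it does use a parameter. Mechanism is counted as one parameter, and if it is coded in several categories the margin narrows.

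**Conclusion.** The point holds for age. The 20 listed items are the 20 counted parameters, age is not among them, and the protocol's own Background gives a reason to test it. Followed as written, the plan cannot do so.

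The likely consequence is a small to modest loss of discrimination. The documents cannot fix its size; the range of 0.00 to 0.03 in AUC depends on the assumed odds ratios, the assumed age split and the assumed independence from the other findings. The conclusion also assumes that the unseen form adds no candidate beyond the 20 that the article counts. The change is worth making because the omission is unexplained and cheap to correct, not because a large loss has been shown.

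**What to change.** In Study procedures, name age as a candidate predictor. Model it preferably as continuous and convert it to categories only when the simplified risk score is built. This is compatible with a yes/no examination form, since age is not an examination item. In Sample size, restate the count as 21 parameters and the minimum as 21 x 10 = 210 fractures. If age is deliberately left out, say so and give the reason.

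Sex may be added as an optional candidate at the same price (22 parameters, 220 fractures), on general grounds only.

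The cost is one routinely available field and a fall from 12.5 to 11.9 events per parameter, or 11.4 with sex as well. A two-term curve for age would use one further parameter: 22 without sex (220 fractures), or 23 with it (230 fractures, 250 / 23 = 10.9 events per parameter). All of these stay within the 250 fractures expected, provided that the fracture share is close to the estimated 50%. With age alone, the guideline would fail below 42% of 500 patients.

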#### Withdrawal of individual subjects

Because this is an observational cohort study, no informed consent will be obtained and therefore withdrawal is unlikely to occur. The treating physician can decide to withdraw a subject from the study for urgent medical reasons.

### Statistical analysis

The data from the academic hospital and the non-academic teaching hospital will be used to develop the model. The data will be assessed by using a multivariable analysis. However, to prevent too optimistic estimates of the accuracy of the diagnostic model, a more liberal p-value for statistical significance will be employed (p = 0.15). Logistic regression modeling will be used to estimate the regression coefficients and thus the log odds of a fracture versus no fracture after which a reduced model will be created by means of a log likelihood ratio test.

The accuracy of the model will be estimated by a goodness of fit test and a ROC curve. If applicable, different models can be compared using the tests mentioned above. The final model will be validated internally through bootstrapping to estimate overfitting in the calibration and discrimination stated above. By averaging the optimism an adjusted model will be generated.

Henceforth, the prediction rule will be validated in a new data set, which will be collected simultaneously in the third hospital; the non-teaching hospital. If necessary, the model will be updated using the data from the validation study, by adjusting the intercept.

Finally, the prediction model will be presented as a simplified risk score which can be used by physicians to determine the need for an X-ray in patients presenting with wrist trauma at the Emergency Department.

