**Methods/Design:**

This study will be a multi-center observational diagnostic study in which the data will be collected cross-sectionally. The study population will consist of all consecutive adult patients (≥18 years) presenting with acute wrist trauma at the Emergency Department in the participating hospitals.

This research comprises two components: one study will be conducted to determine which clinical parameters are predictive for the presence of a distal radius fracture in adult patients presenting to the Emergency Department following acute wrist trauma. These clinical parameters are defined by trauma-mechanism, physical examination, and functional testing. This data will be collected in two of the three participating hospitals and will be assessed by using logistic regression modelling to estimate the regression coefficients after which a reduced model will be created by means of a log likelihood ratio test. The accuracy of the model will be estimated by a goodness of fit test and an ROC curve. The final model will be validated internally through bootstrapping and by shrinking it, an adjusted model will be generated.

In the second component of this study, the developed prediction model will be validated in a new dataset consisting of a population of patients from the third hospital. If necessary, the model will be calibrated using the data from the validation study.

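### As worded, the bootstrap is applied to the already reduced final model, so most of the optimism from choosing among 20 candidates is missed and the model is shrunk too little

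*Protocol article*

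**What the plan says.** The Sample size section of the protocol article starts from a Case Report Form that "lists 20 parameters, therefore requiring a minimum of 200 patients with a distal radius fracture", and expects 500 patients for development.

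The Statistical analysis section sets the order of work. A multivariable logistic model is fitted and reduced by likelihood ratio test, and alternative models may be compared. Then: "The final model will be validated internally through bootstrapping to estimate overfitting in the calibration and discrimination stated above". The next step is: "By averaging the optimism an adjusted model will be generated". The abstract agrees: "The final model will be validated internally through bootstrapping and by shrinking it, an adjusted model will be generated". The opening of Methods/Design likewise makes the developed model the object of the bootstrap.

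The selection threshold is justified in these words: "to prevent too optimistic estimates of the accuracy of the diagnostic model, a more liberal p-value for statistical significance will be employed (p = 0.15".

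After validation in the non-teaching hospital, the Statistical analysis section allows the model to be updated through its intercept, and the result is turned into a simplified risk score for deciding on radiography.

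**The concern.** A bootstrap can only measure the optimism produced by the steps it repeats. If the predictors are held fixed at those that survived selection, every resample treats the set as if it had been known in advance. The advantage gained by picking the best-looking items out of 20 in the same data is then not counted.

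Two results follow. The internally validated AUC looks better than it is, and the shrinkage factor is too close to 1, so predicted risks stay too extreme. The low end matters most, because the risk score is meant to identify patients who may not need an X-ray.

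The stated safeguard does not help. A more liberal p-value retains more noise items and does not reduce optimism, so within the development data the bootstrap is the only step that could measure it.

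**Working it through.** **Inputs from the protocol article**
- Candidates: 20 (Sample size).
- Events rule: "the number of potential determinants should not exceed 10% of the number of events".
- Development sample: "We expect that a period of six months will suffice to include enough patients (500) to formulate the decision rule".
- Fracture prevalence: "is estimated to be about 50" per cent (Sample size).
- Selection: likelihood ratio test, p = 0.15 (Statistical analysis).
- Radiographs per year in the two development hospitals: 550 and 2300 (Sample size).

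**The plan's own figure.** 20 candidates × 10 events = 200 fractures, as stated. At 500 patients, 500 × 0.50 = 250 fractures, or 250 / 20 = 12.5 per candidate. The article gives no optimism or shrinkage figure to reproduce.

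**Scale of selection.** If all 20 items were independent noise, 20 × 0.15 = 3 would be kept on average, and the chance of keeping at least one would be 1 − 0.85^20 = 0.96.

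**Simulation.** Twenty binary candidates, 50% prevalence, backward elimination by likelihood ratio test at p = 0.15. These inputs are assumed because the documents do not give them: 6 to 12 true predictors with log odds ratios of 0.3 to 1.8, latent correlation 0 or 0.3, and item prevalences of 25 to 60%. Each scenario had 100 to 160 simulated studies with 50 to 80 resamples each. The truth was measured in 20,000 new patients.

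- True optimism = apparent AUC − AUC in new patients.
- Bootstrap optimism = mean over resamples of (AUC in the resample − AUC of that resample's model in the original data).
- Shrinkage factor = mean calibration slope of the resample models in the original data. It should equal the slope in new patients.

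Each bootstrap was run in two ways: refitting the selected predictors only (fixed), and repeating the selection (whole).

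| n | True AUC | Optimism: true / fixed / whole | Share found by fixed | Slope: true / fixed / whole |
|---|---|---|---|---|
| 500 | 0.867 | 0.019 / 0.009 / 0.020 | 49% | 0.89 / 0.94 / 0.88 |
| 500 | 0.777 | 0.028 / 0.012 / 0.029 | 42% | 0.86 / 0.94 / 0.86 |
| 500 | 0.711 | 0.035 / 0.016 / 0.037 | 46% | 0.82 / 0.92 / 0.81 |
| 500 | 0.696 | 0.046 / 0.017 / 0.040 | 37% | 0.77 / 0.91 / 0.80 |
| 500 | 0.596 | 0.061 / 0.022 / 0.056 | 37% | 0.60 / 0.87 / 0.68 |
| 400 | 0.774 | 0.033 / 0.014 / 0.036 | 43% | 0.84 / 0.93 / 0.83 |
| 1,425 | 0.874 | 0.007 / 0.004 / 0.007 | 55% | 0.959 / 0.977 / 0.956 |
| 1,425 | 0.788 | 0.008 / 0.005 / 0.011 | 58% | 0.960 / 0.977 / 0.946 |

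The 400 row is the sample that gives the minimum of 200 fractures (200 / 0.50). The 1,425 rows are six months of all radiographs, (550 + 2300) / 2. A separate simulation at 500 patients and about 50% prevalence, with other assumed effects, gave optimism of 0.033 true, 0.015 fixed and 0.031 whole, and slopes of 0.845, 0.93 and 0.848.

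Repeating selection is not exact. In the two weakest-signal scenarios it still falls a little short, but it is much closer than the fixed bootstrap.

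**Effect on a low predicted risk.** Assume risks centred on 50%. After shrinkage by the fixed factor, the remaining slope is true slope / fixed factor. In the second row this is 0.863 / 0.941 = 0.917. A stated 5% has logit −2.944, and −2.944 × 0.917 = −2.70, which is 6.3%. In the weakest scenario, 0.599 / 0.869 = 0.689 and the stated 5% is really 11.6%. Adjusting the intercept changes neither ratio.

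**The threshold.** In a simulation of 500 patients at 41% prevalence (Wald elimination as a proxy), true AUC optimism was 0.027 at p = 0.05, 0.033 at p = 0.15 and 0.040 with no selection.

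**The case against.** **Wording.** The text names what is validated, not what is rerun in each resample, and a condensed article may leave resampling mechanics to a fuller document. A reader might infer that the plan excludes repeating selection. It does not say so. What remains is that the article names the finished model as the object each time, after selection is complete, so an analyst who follows it literally would hold the predictors fixed.

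**Shrinkage.** A reader might also infer that averaging optimism corrects only a performance figure and never touches the coefficients. The documents do not support this. The bootstrap covers calibration as well as discrimination, and the abstract says the model is shrunk. A mean calibration slope is a legitimate shrinkage factor. Here it would come from the wrong bootstrap.

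**External validation.** The plan requires validation in a third hospital, with a data set of similar size, before the score is presented. Residual overfitting would be revealed there, and care during the study is as usual, so the internal AUC alone leads to no withheld X-ray. This lowers the severity. It does not remove the point, because the Statistical analysis section confines updating to the intercept.

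**Threshold.** The effect of p = 0.15 is small (0.033 against 0.027), and a small check of 80 data sets found true AUC of 0.750 at p = 0.05 and 0.752 at p = 0.15. The choice of threshold therefore does no harm to accuracy. Only the reason given for it fails.

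**Sample size.** Consecutive enrolment could yield up to about 1,425 patients, where the gap is small. The only stated target is 500.

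**Conclusion.** The point holds on the plain reading of the text, with moderate severity. At the planned 500 patients, bootstrapping the reduced model finds about 37 to 49% of the true AUC optimism. At a true AUC near 0.75 to 0.78 that is 0.012 to 0.015 against 0.028 to 0.033, with a shrinkage factor of 0.93 to 0.94 where about 0.84 to 0.86 is needed.

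The direction was the same in every scenario. The size rests on assumed effects, correlations and item prevalences, is larger when the signal is weak, and becomes small near 1,425 patients.

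The stronger conclusion that the plan is invalid until this is changed is not supported, since shrinkage and external validation are both planned. The rationale for p = 0.15 is wrong as stated, but the threshold can stay.

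**What to change.** In the Statistical analysis section, replace the internal validation sentences with text such as:

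> The complete modelling procedure (all 20 candidates, likelihood ratio reduction at p = 0.15 and any comparison of models) is repeated in every bootstrap sample. The mean optimism from this procedure is subtracted from the apparent c-index. The coefficients are multiplied by the mean bootstrap calibration slope and the intercept is then re-estimated.

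Change the reason for p = 0.15 to reducing the risk of losing true predictors, and delete the claim that it prevents optimistic accuracy estimates. Align the abstract and the opening of Methods/Design.

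The cost is a few sentences and more computing time, with no new data. The reported internal AUC falls by about 0.02. In the five scenarios at 500 patients the difference between the two bootstraps ran from 0.020 − 0.009 = 0.011 to 0.056 − 0.022 = 0.034.

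### The external update is limited to the intercept, which cannot correct a calibration slope that differs from 1 in the third hospital; logistic recalibration is a cheap improvement

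*Protocol article*

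**What the plan says.** The Statistical analysis section builds a logistic model in two hospitals, reduces it at a liberal significance level of 0.15, and corrects it before it leaves the development data: "The final model will be validated internally through bootstrapping to estimate overfitting in the calibration and discrimination stated above", followed by "By averaging the optimism an adjusted model will be generated". The Abstract calls this step shrinkage: "The final model will be validated internally through bootstrapping and by shrinking it, an adjusted model will be generated".

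The adjusted model is then tested in the third, non-teaching hospital. The Study procedures section presents this as domain validation, in a deliberately different setting. On what follows, the Abstract leaves the method open: "If necessary, the model will be calibrated using the data from the validation study". The Statistical analysis section closes it: "If necessary, the model will be updated using the data from the validation study, by adjusting the intercept". The result is to be presented as a simplified risk score that helps physicians decide on an X-ray.

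**The concern.** Calibration in a new hospital can fail in two ways. Predictions can be too high or too low on average, which an intercept shift repairs. They can also be too extreme or too moderate (slope below or above 1), which an intercept shift cannot repair. If the two settings have similar fracture rates, the intercept hardly moves and a slope error remains almost in full, although the model may be reported as updated.

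The low end of the risk scale is where an X-ray would be withheld. With a slope below 1, the true fracture risk there is higher than the risk shown. Naming the intercept as the update is a stated choice of method, so this is not a detail merely left to an analysis plan.

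**Working it through.** **Inputs from the article.** The Sample size section gives 20 candidate parameters, at least 10 events per candidate, 500 development patients, about 50% fractures, and a validation set of equal size (so about 500). The Statistical analysis section gives selection at p = 0.15, bootstrap adjustment and an intercept-only update.

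**Step 1, the article's own figure.** 20 / 0.10 = 200 fractures, as stated. The planned 500 patients give 500 x 0.50 = 250 fractures, or 250 / 20 = 12.5 per candidate.

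**Step 2, what shrinkage achieves.** The article gives no predictor effects, so these are assumptions: 20 correlated binary candidates, 50% prevalence and true AUC of 0.70, 0.77 or 0.85. Selection was backward at p = 0.15, with Wald tests standing in for likelihood ratio tests. It was repeated within each of 30 bootstrap samples. There were 60 runs per setting, and the slope was measured in a large sample from the same population.

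| AUC | Mean slope, no shrinkage | Mean slope after shrinkage (SD) | Runs with slope below 0.9 after shrinkage |
|---|---|---|---|
| 0.70 | 0.77 | 0.98 (0.13) | 30% |
| 0.77 | 0.83 | 1.00 (0.11) | 20% |
| 0.85 | 0.87 | 1.02 (0.11) | 17% |

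With 60 runs, the standard error of the last column is about sqrt(0.30 x 0.70 / 60) = 6 percentage points at most. The shrinkage works on average. The slope in a single sample still varies in both directions: it was below 1 in 63%, 50% and 42% of runs, and so at or above 1 in 37%, 50% and 58%. Differences in predictor effects between hospitals would add to this spread; the article gives no figure for them.

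**Step 3, what a remaining slope error means.** With about 50% fractures and predictions centred there, the intercept shift is zero and true risk = expit(slope x logit(displayed risk)). For example, logit(0.02) = -3.892; times 0.8 is -3.113; expit gives 4.3%.

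| Displayed | True, slope 0.8 | True, slope 0.9 | True, slope 1.1 |
|---|---|---|---|
| 2% | 4.3% | 2.9% | 1.4% |
| 5% | 8.7% | 6.6% | 3.8% |

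The displayed values are illustrations, since the article states no cut-off. How many patients reach them depends on discrimination. After shrinkage and an intercept update, no simulated patient had a displayed risk under 10% at AUC 0.70 or 0.77; at AUC 0.85, 3.4% did.

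**Step 4, can 500 validation patients show a slope error?** Each setting used 600 simulated data sets, with the SD of the linear predictor at 1.2 or 1.8. A direct test of slope = 1 has power of 17-24% at slope 0.9, 30-42% at 0.85, 53-62% at 0.8 and 88-96% at 0.7. That is moderate at best, so the estimate and its interval are more informative than the test alone.

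**The case against.** The strongest reply is that the plan already treats overfitting where it arises. Bootstrap adjustment and shrinkage come before external validation and target exactly the too-extreme predictions that a selected model produces. This stands, and it rules out two stronger readings. A reader might infer that calibration is corrected only by the intercept; that is true of the external update, not of the plan. A reader might also infer that too-extreme predictions are to be expected. Mean slopes of 0.77-0.87 describe an unshrunk model, which is not what the article plans to validate.

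A third tempting reading is that the goodness-of-fit test decides whether an update is needed. The article does not say so. "The accuracy of the model will be estimated by a goodness of fit test and a ROC curve" stands in the account of model development, and no trigger for updating is given; an article may leave that to a fuller document. Nor does "different models can be compared using the tests mentioned above" establish that models are ranked by a goodness-of-fit p-value, because the tests referred to can include the ROC curve and the likelihood ratio test.

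It is also fair to say that harm is not demonstrated. Adjusting the intercept, or the intercept with a positive slope, leaves the ranking of patients and the AUC unchanged. If the score's cut-off were set by observed sensitivity, a slope error would send no additional fracture home. Finally, choosing the update by a test shares the power limit shown above.

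What the reply does not remove is that shrinkage uses development data alone and cannot detect different predictor effects in the non-teaching hospital, and that the one external update named could not correct a slope error found there.

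**Conclusion.** The point holds as a conditional, inexpensive improvement, not as a demonstrated error. Intercept adjustment corrects average risk only. After the planned shrinkage the slope should be about 1 on average in the development population, with roughly a 17-30% chance of falling below 0.9 under the assumed effects and a further, unquantified risk from the change of hospital type. A remaining slope of 0.8-0.9 would understate a 2% or 5% risk by a factor of about 1.3 to 2.1 (6.6/5 = 1.3; 4.3/2 = 2.1). A slope above 1 would overstate low risks instead. The consequence depends on displayed risks or a risk-based cut-off being used to withhold an X-ray, and on the model discriminating well enough to produce such low risks. Without a stated cut-off, the number of patients affected cannot be calculated.

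**What to change.** In the third hospital, report the performance of the shrunken, un-updated model as the external validation result, including the calibration intercept and slope with 95% CIs.

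In the Statistical analysis section, replace the intercept-only wording with logistic recalibration. Choose between no update, intercept only, and intercept plus slope by likelihood ratio test. Report the slope estimate and its interval whichever option is chosen, because the slope test has only about 53-62% power at slope 0.8 with 500 patients. Label any updated model as not yet externally validated.

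The cost is a change of wording and one additional two-parameter logistic fit, with no new patients or measurements. The downside is that one more parameter is estimated from the validation data.
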